#### **2.2.1.2 Secondary Efficacy Endpoints**

- CD4 counts at all visits in the study, absolute numbers of CD4 counts, and treatment emergent changes of CD4 counts from mean of Screening and Visit 2.
- Change (and percent change) in CD4 count from Visit 5 (discontinue ART) to Visits 6, 7, 8, 9 and 10 (End of Study).
- CD8 counts at all visits in the study, absolute numbers of CD8 counts, and treatment emergent changes of CD8 from mean of Screening and Visit 2.
- Change (and percent change) in CD8 count from Visit 5 (discontinue ART) to Visits 6, 7, 8, 9 and 10 (End of Study).

For each individual subject both the absolute and relative changes in CD4 and CD8 values registered at Visit 5, and at Visit 9 (or the last value before reinitiated ART, if ART reinitiated before Visit 9) will be compared with the corresponding values registered at Week 28 (ART discontinued) and Week 52 (or last visit before ART re-initiation) in the initial study CT-BI Vacc-4x 2007/1 (EudraCT Number 2007-006302-13).

- DTH (both induration and erythema) at Visit 2 and Visit 4, in terms of observed areas ( $\text{mm}^2$  length x height) and also in terms of a positive test, defined as an area  $\geq 10\text{mm}^2$  DTH-tests, both areas and number of positive tests registered at Visit 2 will be compared with the corresponding values registered at Visit 4.

In addition the values for these DTH parameters at Visit 4 will be compared with the DTH response reported at Week 18 in the initial study CT-BI Vacc-4x 2007/1 (EudraCT Number 2007-006302-13).

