## **3 STUDY DESIGN**

### **3.1 Overall Study Design and Flow Chart**

The study is an open label, multicenter, follow-up, re-boosting study of subjects who previously completed the immunization regimen with Vacc-4x active and stopped ART (at Week 28) in the CT-BI Vacc-4x 2007/1 Study (EudraCT Number 2007-006302-13). No restart of ART is required. The subjects will be re-boosted with two immunizations (Visit 2 and Visit 3) of Vacc-4x, 1.2 mg peptides (12 mg/mL), with a 2 week interval between immunizations.

At Visit 5 ART medication (if being used) will be stopped in subjects whose CD4 count  $\geq 350 \times 10^6/\text{L}$ , for a 16 week period. At Week 29 ART will be restarted, according to the Investigator and subject's decision, and the subjects will be followed for an additional 8 weeks (End of Study; Visit 10).

DTH will be measured at Visit 2, and at Visit 4 (3 weeks after the second re-boosting immunization).

Viral load, CD4 and CD8 counts will be measured at all study visits. T-cell responses will be measured at Visits 2, 4, 6, 9 and 10 (End of Study) both by ELISPOT, T-cell proliferation assay and intracellular cytokine staining.

Vital signs and clinical laboratory tests will be done at all study visits.

Monitoring of AEs and concomitant medications will be done continuously from the time of signing ICF through the End of Study.

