### **6.3.2.4 Visit 5**

This visit should be 84 ( $\pm 3$ ) days from Visit 2.

If on ART, the subject will be instructed to now stop ART if their CD4 count is  $\geq 350 \times 10^6/\text{L}$  and virally controlled (undetectable VL [ $<50$ copies] over a period of three months on a stable antiretroviral regimen with no more than one blip allowed). If the CD4 count is  $<350 \times 10^6/\text{L}$  and/or the virus is not controlled, the subject will be instructed to remain on ART. The instruction will be based on the results of CD4 count and viral load from this visit. As soon as possible when these

results are available, and at the latest within one week after this visit, the investigator will contact the subject by phone and tell the subject to stop ART, or not to stop ART. Stopping of ART will be done according to local guidelines and their current clinical judgment and based on the individual ART the subjects are receiving. Subjects will be instructed to write down the date(s) when stopping ART and take this information to the investigator at the next visit.

The Investigator needs to see the results from the blood sampling at Visit 5 before the subject can stop ART. The information to the subject that he/she can stop ART and instructions on how to do this can be made by telephone. It is important that the treatment interruption period has a full 16 week duration.

The following procedures will be performed:

- Review of concomitant medications and AEs.
- Physical examination including weight.
- Vital signs (blood pressure, heart rate).
- Clinical chemistry and hematology.
- Viral load, CD4 and CD8 counts.

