### **10.3 Populations to be Analyzed**

The following populations will be used in the analyses:

**Safety:** All subjects who receive at least one re-boosting immunization will be included within the safety population. All safety analyses will be conducted on the safety population.

**Intention to treat (ITT):** All subjects who receive at least one re-boosting immunization and have any post-baseline efficacy data will be included in the ITT population. Unless otherwise indicated, all efficacy analyses will be conducted on the ITT Population.

**Per protocol (PP):** All ITT subjects who receive two re-boosting immunizations, discontinue ART at Visit 5 (as planned) and who do not incur a major protocol violation that would challenge the validity of their data will be included within the PP population. All efficacy analyses will also be conducted on the PP population.

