#### **10.6 Statistical Methods**

In general continuous variables will be described using number of observations (n), mean, standard deviation (SD), geometric mean, minimum, maximum, median, and quartiles. Categorical data will be presented using counts (n) and percentages (%).

All statistical analyses will be performed using appropriate procedures in SAS Software Version 9.2 or higher. Significance of effects will be determined by two-sided tests with p-value < 0.05.

All analyses will be carried out after all participants have completed Visit 10 (or early withdrawal from study) and the study database has been authorized by the Sponsor as complete and final, and protocol deviations have been identified.

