### **10.6.2.2 Secondary Efficacy Endpoints**

The following endpoints (based on continuous data types) will be compared (for within subject comparisons) using the Wilcoxon signed rank test:

- CD4 counts at all visits, absolute numbers, and treatment emergent changes from the mean of Screening and Visit 2 data.
- Change (and percent change) in CD4 count from Visit 5 (discontinue ART) to Visit 6, 7, 8, 9 and 10 (End of Study).
- CD8 counts at all visits, absolute numbers, and treatment emergent changes from the mean of Screening and Visit 2 data.
- Change (and percent change) in CD8 count from Visit 5 (discontinue ART) to Visit 6, 7, 8, 9 and 10 (End of Study).

For each individual subject both the absolute and relative changes in CD4 and CD8 values registered at Visit 9) will be compared with the corresponding values registered at Week 28 (ART discontinued) and Week 52 (or last visit before ART re-initiation) in the initial study CT-BI Vacc-4x 2007/1 (EudraCT Number 2007-006302-13).

- DTH (both induration and erythema) at Visit 2 and Visit 4, in terms of observed areas (mm^2 length x height), areas at Visit 2 will be compared with the corresponding values registered at Visit 4. In addition the values for these DTH parameters at Visit 4 will be compared with the DTH responses reported at Week 18 in the initial study CT-BI Vacc-4x 2007/1 (EudraCT Number 2007-006302-13).

The following endpoints (based on binary data types) will be compared (for within subject comparisons) using McNemar's test:

- DTH (both induration and erythema) at Visit 2 and Visit 4, in terms of a positive test, defined as an area  $\geq 10\text{mm}^2$ . The number of positive tests registered at Visit 2 will be compared with the corresponding values registered at Visit 4. In addition the values for these DTH parameters at Visit 4 will be compared with the DTH responses reported at Week 18 in the initial study CT-BI Vacc-4x 2007/1 (EudraCT Number 2007-006302-13).

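### The ITT default admits subjects with no ART stop at Visit 5 to the CD4/CD8 comparison with the initial study and biases it towards an apparent re-boost benefit

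*Protocol*

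**What the plan says.** Section 10.6.2.2 lists "Change (and percent change) in CD4 count from Visit 5 (discontinue ART) to Visit 6, 7, 8, 9 and 10 (End of Study", and the same for CD8, among the continuous endpoints that "will be compared (for within subject comparisons) using the Wilcoxon signed rank test". Section 10.6 adds: "Significance of effects will be determined by two-sided tests with p-value < 0.05".

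A separate paragraph brings in the initial study. In section 2.2.1.2 it begins "For each individual subject both the absolute and relative changes in CD4 and CD8 values registered at Visit 5, and at Visit 9". It sets these changes against the values at Week 28, when ART was stopped, and at Week 52 or the last visit before ART was resumed. Section 10.6.2.2 repeats this in shortened form, naming only Visit 9 on the side of the present study and dropping the substitution for subjects who restart ART before Visit 9.

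Neither section names an analysis set. Section 10.3 then decides: "Unless otherwise indicated, all efficacy analyses will be conducted on the ITT Population". Membership of that set does not depend on ART: "All subjects who receive at least one re-boosting immunization and have any post-baseline efficacy data will be included in the ITT population".

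The design allows two kinds of subject with no ART stop at Visit 5:

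- **Staying on ART.** Under section 6.3.2.4, if CD4 is below 350 × 10⁶/L and/or the virus is not controlled, "the subject will be instructed to remain on ART".
- **Already off ART.** Section 3.1 says "At Visit 5 ART medication (if being used) will be stopped". Section 4.2 does not require ART to have been restarted after the initial study, and Table 1 gives ART status at entry as on or off.

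**The concern.** Section 4.1 requires every participant to have stopped ART at Week 28 of the initial study. The reference change is therefore always a change after an interruption. Section 1.4 reports, for an earlier Phase II study, that CD4 counts fell when ART was interrupted. A subject who stays on ART after Visit 5 has no such fall, and a subject long off ART is past the fall that follows a stop. Pairing either with the change after Week 28 gives a difference in the direction of smaller CD4 loss after re-boosting, whether or not the vaccine does anything.

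This is a systematic shift, so more subjects make a false positive more likely, not less. The protocol guards against the same problem elsewhere: section 2.2.1.1 limits the viral load set point to subjects who discontinue ART according to protocol and do not resume it until Visit 9. The CD4/CD8 comparison has no such limit.

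**Working it through.** The protocol states no effect size, SD or power for this endpoint. Its 30 to 40 subjects (section 10.1) are an estimate of availability, so there is no figure to reproduce. The check is of direction, and of size under stated assumptions.

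**Direction.** Let p be the share of non-stoppers, D the mean CD4 decline after an ART stop, and D₀ the mean decline in non-stoppers between Visit 5 and Visit 9. With no re-boost effect:

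- Mean change in the initial study: −D for everyone.
- Mean change in this study: −(1 − p)·D − p·D₀.
- Mean paired difference: p·(D − D₀), which is p·D when D₀ = 0.

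**Inputs from the protocol.** n = 30 to 40; Wilcoxon signed rank; two-sided 0.05. The nominal favourable tail is therefore 2.5%.

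**Assumed inputs, not in the protocol.** D = 100 or 200 × 10⁶/L; D₀ = 0; p = 0 to 30%; no re-boost effect; and the same D in both interruptions, although the windows are 52 − 28 = 24 weeks and 16 weeks. The last assumption isolates the effect of non-stoppers. Two spreads were used:

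- **A:** SD of change 150, changes independent between studies. SD of the paired difference = 150 × √2 ≈ 212.
- **B:** SD of change 120, correlation 0.5. SD of the paired difference = 120 × √(2 × (1 − 0.5)) = 120.

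**Comparison with Week 28 to Week 52**, by simulation (4,000 trials per cell for A, 2,000 for B):

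| Non-stoppers | Bias p·D (× 10⁶/L) | Favourable rejections, A | Favourable rejections, B |
|---|---|---|---|
| 0% | 0 | 2.1–2.5% | 2–3% |
| 10% | 10 to 20 | 3.8–7.4% | 5–10% |
| 20% | 20 to 40 | 6.7–16.5% | 11–33% |
| 30% | 30 to 60 | 10.3–31.5% | 21–63% |

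Each range covers n = 30 to 40 and D = 100 to 200. The simulated mean differences under A agree with p·D: 9.7–19.9 at 10%, 19.8–40.2 at 20% and 29.9–60.4 at 30%. A and B differ mainly because the paired difference is less variable under B, so the same bias is easier to detect.

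**Visit 5 change tested against zero**, under A with 30% non-stoppers. The mean moves from −100 to 0.7 × (−100) = −70, or from −200 to −140. The chance of a significant decline falls from 93–98% to 65–77% when D = 100 and stays near 100% when D = 200. The decline is diluted, and no benefit is declared.

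**The case against.** The strongest reply is that the protocol already plans the restricted analysis. Section 10.3 repeats every efficacy analysis in the per-protocol population, which requires ART to be discontinued at Visit 5. Section 10.5.2 promises subgroup analyses of the efficacy endpoints that exclude subjects or data by ART timing, with details left to the SAP. This stands, and a reader who inferred that no analysis in stoppers exists would be wrong. It does not change which analysis leads: section 10.3 makes ITT the default and per-protocol the addition, and section 10.5.2 does not alter that order. The per-protocol set also drops subjects for a missed re-boost or a major violation, so it is narrower than this question needs.

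A reader might also infer that the Visit 5 change endpoint itself tests a re-boost benefit. It does not. It is a within-subject change, and non-stoppers only weaken the decline it shows. The false benefit arises in the cross-study paragraph alone.

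The wording does hint at an interruption endpoint, since Visit 5 is labelled as the ART stop and section 2.2.1.2 substitutes the last value before ART is resumed. But that substitution covers subjects who stop and restart early, not those who never stop, and a label does not name a population.

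The size is open to attack, and most of that attack stands. Of the 88 vaccinated subjects who stopped ART, 56 (64%) stayed off it to Week 52 of the initial study. That does not estimate how many enter this later study off ART. Sections 1.5.3 and 1.6 describe subjects as on ART during immunization, and entry requires CD4 of at least 400 × 10⁶/L, so the share could be small. Zero change in untreated subjects is also generous: section 1.1 says CD4 falls in the course of infection, which makes D₀ positive and the bias smaller for them.

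**Conclusion.** The concern holds for the comparison with Week 28 to Week 52. In its default analysis set, that comparison can pair a change without an ART stop with a change after one. If non-stoppers lose fewer cells than stoppers, the bias runs towards an apparent re-boost benefit, by about p·D. With assumed declines of 100–200 × 10⁶/L, SD 120–150 and correlation 0–0.5, the favourable false-positive rate goes from about 2.5% to roughly 4–10% at 10% non-stoppers and 7–33% at 20%. The figures at 30%, up to 63%, need a high share, the larger decline and the smaller spread together. They should not be read as a forecast, because the protocol supports none of those values.

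This is a secondary endpoint in an open, uncontrolled study, and the primary viral load endpoint is not affected. The point is worth correcting because the error favours the product and is easy to remove.

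**What to change.** In sections 2.2.1.2 and 10.6.2.2, state that the leading analysis of CD4/CD8 change from Visit 5, and of its comparison with Week 28 to Week 52, is in subjects who were on ART at Visit 5 and stopped it under section 6.3.2.4. Report ITT as supportive. Summarise subjects who stayed on ART and subjects off ART from entry separately, without pairing them with the initial-study interruption. Bring the shortened paragraph in section 10.6.2.2 into line with section 2.2.1.2, so that both define the same change. This uses the exception that section 10.3 already allows and matches the limit set for viral load.

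The cost is one sentence in each section, no change to study procedures, and somewhat fewer subjects in a secondary comparison. There is also a statistical cost. Stopping depends on Visit 5 CD4 and viral control, and that CD4 value is also the baseline of the change. Selecting on it brings some regression to the mean, which can exaggerate the later decline. The report should say so when interpreting the result.

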### **10.6.3 Safety Analyses**

Safety will be assessed through the collection of AE reports, assessing virologic suppression, vital signs, and laboratory evaluations that are commonly employed in clinical studies. Week 1 safety data will be used for comparison with the data obtained during the study period. Summary statistics will be prepared for measured values and change from Visit 2 values. Virologic suppression will be assessed between the timing of ART interruption and ART re-initiation. Summaries of treatment-emergent clinically important abnormalities in vital signs and laboratory data will be provided. No statistical testing will be performed on safety parameters.

#### **10.6.3.1 Adverse Events**

For presentation, AE verbatim text will be coded into a Medical Dictionary for Regulatory Activities (MedDRA) term, and classified by System Organ Class (SOC) and preferred term. AEs will then be summarized and grouped by SOC and preferred term. Results will be displayed in order of decreasing frequency, both across SOC and within each SOC term. AEs with onset on or after the start of study medication are considered treatment-emergent. AEs reported prior to treatment administration will be reported separately from treatment-emergent AEs.

In addition, summaries will be provided by incidence, severity (mild, moderate, severe), and relationship to study medication (Related, Unrelated). "Possibly Related", "Probably Related" and "Definitely Related" or relationship is missing will be grouped as "Related."

SAEs and AEs leading to discontinuation will be listed.

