#### **2.1.2 Secondary Objectives**

- To evaluate the effect of a re-boost with Vacc-4x on CD4 counts and CD8 counts.

- To assesses *in vivo* immunogenicity of Vacc-4x by evaluation of DTH and to compare the DTH response to the DTH response observed in the initial study; CT-BI Vacc-4x 2007/1 (EudraCT Number 2007-006302-13).
- To evaluate the safety and tolerability of re-boosting with Vacc-4x.

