### **2.2.2 Safety Endpoints**

- Proportion of subjects who experience similar virologic suppression 8 weeks after re-initiation of ART (Visit 10) as before ART interruption (Visit 5 value).
- AEs, recorded continuously from screening to Visit 10 (End of Study).
- Vital signs (heart rate, blood pressure) at Screening, and selected visits through Visit 10 (End of Study).
- Clinical laboratory evaluations (clinical chemistry, hematology) at screening, and selected visits through Visit 10 (End of Study); absolute values and treatment emergent changes from mean Screening and Week 1.

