### **6.3.2.2 Visit 3**

This visit should be 15 ( $\pm 2$ ) days from Visit 2.

The following procedures will be performed in the following order (it is important that all blood samples are taken before administration of study treatments):

- Review of concomitant medications and AEs.
- Vital signs (blood pressure, heart rate).
- Urine pregnancy test (all females of child bearing potential).
- Clinical chemistry and hematology.
- Viral load, CD4 and CD8 counts.
- Intradermal administration of Leukine®.
- Intradermal administration of Vacc-4x, 10 to 20 minutes after administration of Leukine®.

The subject should remain in the clinic for 1 hour after the administration of study drug to be monitored for adverse reactions to the immunization.

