### **8.1.4 Recording of Adverse Events and Serious Adverse Events**

From the point of signing the informed consent form (ICF) to the first re-boost (first administration of study treatment), any worsening of an existing or new medical condition must be recorded on the Medical History CRF page. Following administration of study medication up to the Visit 10 (End of Study), any worsening of an existing or new medical condition must be recorded as an AE on the CRF. The Investigator should review all documentation (e.g., hospital progress notes, laboratory, and diagnostic reports) relative to the event being reported. The Investigator will then record all relevant

information regarding an AE/SAE on the appropriate CRF page. The Investigator will evaluate AEs using the following guidelines:

- Description of event (if the event consists of a cluster of signs and symptoms, a diagnosis should be recorded [e.g., flu syndrome] rather than each sign and symptom).
- Onset date and time.
- Stop date and time.
- Intensity should be described according to the Division of AIDS Table for Grading Severity of Adult and Pediatric Adverse Events, Version 1.0 December 2004; Clarification August 2009 (Appendix 15.1) as Mild (Grade 1), Moderate (Grade 2), Severe (Grade 3), or Life threatening (Grade 4). Intensity is defined as one of the following:
  - Mild: transient or mild discomfort; no limitation in activity; no medical intervention/therapy required.
  - Moderate: mild to moderate limitation in activity- some assistance may be needed; no or minimal medical intervention/therapy required.
  - Severe: marked limitation in activity, some assistance usually required; medical intervention/therapy required; hospitalization is possible.
  - Life-threatening: extreme limitation in activity, significant assistance required; significant medical intervention/therapy required; hospitalization or hospice care probable.

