It is important to distinguish between SAEs and severe AEs. Severity is a measure of intensity, whereas seriousness is defined by the criteria provided in [Section 8.1.2](#). An AE of severe intensity need not necessarily be considered serious. For example, a migraine headache that incapacitates a subject for many hours may be considered a severe AE, whereas a stroke that results in a limited degree of disability may be considered mild, but should be reported as an SAE. If any parameter within a record of an AE changes, a fresh record should be made in the CRF. For example, when the severity of the AE increases, the AE should be recorded as resolved at the existing severity level and re-entered into the CRF with a new start date reflecting the first date of the increased severity.

- Seriousness (see definition of an SAE, [Section 8.1.2](#)).

The Investigator must record whether or not the AE meets the definition of serious. If the event is serious, the Investigator must complete an SAE Report Form.

- Relationship to study drug.

The Investigator must make a causality assessment for all AEs and must decide whether there is a reasonable possibility that the AE may have been caused by the study drug. If there is any valid reason for suspecting that there is a causal relationship between the AE and the study drug, the AE should be judged “possibly related,” “probably related,” or “definitely related”

to study drug. Unless an AE can be excluded from causality, it must be judged “possibly related” to study drug rather than “not related” to study drug.

- **Definitely Related:** An AE is considered definitely related when there is clear evidence that the event was caused by test article use. A definitely related event has a strong temporal relationship and an alternative cause is unlikely (other possible contributing factors can be ruled out).
  - **Probably Related:** An AE is considered probably related when there is a reasonable possibility that the event is likely to have been caused by test article use. The AE has a timely relationship to the study procedure(s) and follows a known pattern of response, but a potential alternative cause may be present.

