##### **10.5.2 Subgroup Analyses**

For the reporting of efficacy endpoints subgroup analyses will be performed. The definition of subgroups (either certain subjects excluded or part of their data excluded) will be based on the timing of when a subject is on or off ART during their participation in the study. This will be further documented within the Statistical Analysis Plan.

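### Adverse events from first dose to Visit 10 form one treatment-emergent class with no summary by ART period, so the planned tables cannot separate events near the re-boost from events during ART interruption or restart

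*Protocol*

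**What the plan says.** The safety objective in 2.1.2 is "To evaluate the safety and tolerability of re-boosting with Vacc-4x". Section 2.2.2 defines the AE endpoint as "AEs, recorded continuously from screening to Visit 10 (End of Study"), and 8.1.4 states the AE recording duty after dosing in these terms: "Following administration of study medication up to the Visit 10 (End of Study), any worsening of an existing or new medical condition must be recorded". In 10.6.3.1, "AEs with onset on or after the start of study medication are considered treatment-emergent"; no end of the window is given and ART status is not mentioned. That section summarises AEs by system organ class and preferred term, and by incidence, severity and relationship (Related or Unrelated), with listings of serious AEs and AEs leading to discontinuation.

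Background treatment changes inside the window. At Visit 5 (6.3.2.4), "If on ART, the subject will be instructed to now stop ART", subject to CD4 count and viral control. At Visit 9 (6.3.3.4) restart is recommended. The protocol recognises that this timing matters, but 10.5.2 confines the resulting split: "For the reporting of efficacy endpoints subgroup analyses will be performed", with subgroups defined by when a subject is on or off ART.

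On causality, 8.1.4 sets a default: "Unless an AE can be excluded from causality", it is scored as possibly related. Section 10.6.3.1 then groups possible, probable, definite and missing relationship as Related.

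**The concern.** The objective asks how well the re-boost is tolerated. There are two doses, about two weeks apart, at the start of a 36-week follow-up. Most of that follow-up concerns something else: withdrawal of ART and then its resumption. Section 1.6 itself links interruption of ART for extended periods to increased morbidity and mortality, and 4.4.1.3 gives examples of clinical and laboratory features that may follow from stopping.

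A single count per preferred term from first dose to Visit 10 mixes three situations: recent vaccination on stable background treatment, time off ART, and the weeks after restart. With no control arm, nothing else in the AE tables tells them apart. A reader could draw a clear AE answer neither about the period around the re-boost nor about the interruption.

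**Working it through.** **Inputs.** Days are counted from Visit 2, the first re-boost.
- Last re-boost: Visit 3, Day 15 (6.3.2.2).
- ART stop: Visit 5, Day 84 ± 3, with the instruction given up to one week later (6.3.2.4).
- Restart recommended: Visit 9, Day 196 ± 7 (6.3.3.4).
- End of study: Visit 10, Day 252 ± 7 (6.3.4.1).

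**Step 1: the protocol's own period lengths.** (196 − 84)/7 = 16.0 weeks and (252 − 196)/7 = 8.0 weeks. Both agree with 6.1.

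**Step 2: share of the treatment-emergent window, for a subject who stops at Visit 5.**
- Before the stop: 84/252 = 33.3%.
- ART-free: 112/252 = 44.4%.
- After planned restart: 56/252 = 22.2%.
- After the stop in total: (112 + 56)/252 = 168/252 = 66.7%.

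**Step 3: distance from dosing.** The window runs 252 − 15 = 237 days past the last re-boost. Of these, 84 − 15 = 69 precede Visit 5 and 168 follow it.

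**Step 4: sensitivity of the two-thirds figure.**
- All visits at the early end of their windows: (245 − 81)/245 = 66.9%.
- All visits at the late end: (259 − 87)/259 = 66.4%.
- Stop one week after Visit 5: (252 − 91)/252 = 63.9%.
- The restart date moves days between the second and third periods but does not change the total after the stop.

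**Step 5: time is not events.** The protocol gives no AE rates, so the share of AEs can only be illustrated under assumptions.
- Constant event rate: 64% (stop at Day 91) to 67% (stop at Day 84) of treatment-emergent AEs start after the stop.
- Rate 1.5 to 3 times higher while off ART (assumed): about 70% to 82%.
- Rate 2 or 3 times higher before the stop, because injection-site reactions cluster around dosing (assumed): 168/(2 × 84 + 168) = 50%, or 168/(3 × 84 + 168) = 40%.

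Under each of these assumptions a substantial part of the AE count comes from after the stop, but its size is unknown.

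**Step 6: does the relationship table separate the periods?** Section 8.1.4 asks for causality against study drug only; no category attributes an event to ART interruption or restart. *Not related* requires a known cause, doubtful events default to *possibly related*, and missing counts as Related. Some separation results, since the definition of *possibly related* refers to a reasonable time after use, but it depends on individual judgement in an open study.

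**The case against.** The strongest reply has five parts.

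1. *Treatment-emergent* is a standard timing definition, and columns by onset period are ordinary SAP detail that would contradict nothing in the protocol. This is true, and it means the text is not an error in itself. What remains is that 10.6.3.1 does list its AE summaries, and that 10.5.2 introduces an ART-timing split and restricts it to efficacy.

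2. Some effects of viral rebound never reach the AE tables. Section 8.1.1 excludes signs and symptoms of the disease under study unless more severe than expected, and 8.1.3 says laboratory abnormalities are usually not recorded as AEs. This stands. It limits any inflation of the AE counts, and it also makes the AE burden of interruption less visible.

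3. The interruption is assessed elsewhere: virologic suppression at Visit 10 against Visit 5 (10.6.3.2), CD4 change from Visit 5 at each later visit (10.6.2.2), and vital signs by visit (10.6.3.3). This stands too. The gap concerns AEs, not the consequences of interruption as a whole.

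4. Not everyone stops. Subjects may enter off ART, may fail the Visit 5 conditions, or may not restart. This stands; the two-thirds figure applies only to subjects who stop at Visit 5.

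5. Assigning the first period to the re-boost and the second to the interruption would attribute cause by calendar and could remove late vaccine effects from the re-boost assessment. This stands and shapes the fix.

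A reader might infer that interruption events are counted against the re-boost, so that its toxicity is overstated. The documents do not support this: the definition assigns no cause, an event months after dosing may fail the timing test for *possibly related*, and no AE rates are given. Nor do they support saying that the risk of interruption is hidden, given the analyses under point 3.

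**Conclusion.** The point holds as a limit on what the planned AE tables can show. For subjects who stop ART at Visit 5, about two thirds of the nominal window (64% to 67% across the visit windows and a one-week delay in stopping) lies after the stop, and no listed AE summary distinguishes that time from the time around the re-boost. The relationship table distinguishes it only weakly. The figure is a share of scheduled follow-up, not of events, and assumes follow-up to Visit 10. The direction and size of any effect on the apparent tolerability of the re-boost cannot be derived from the protocol. This is an inexpensive improvement to the safety reporting, not a correction of a wrong analysis.

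**What to change.** Keep the overall treatment-emergent and relationship tables in 10.6.3.1 as they are. Add descriptive columns for treatment-emergent, related and serious AEs by onset period: first dose to actual ART stop, ART-free, and after actual ART restart. Show subjects who were off ART throughout, and subjects who never stopped ART, separately. Extend the ART-timing split in 10.5.2 to AEs. Present the periods side by side and state that period of onset does not establish cause.

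The data are already planned: AE onset dates (8.1.4), ART stop dates (6.3.3.1) and concomitant medication dates (5.2). The restart date has no recording step of its own at Visit 9 or 10, so confirm that it is captured with the concomitant medications. The cost is a little more table work and sparse cells with 30 to 40 subjects, so the columns should remain descriptive. No clinical procedure changes.
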